# Comparing the effect of auricular acupressure and body acupressure on pain and duration of the first stage of labor: study protocol for a randomized controlled trial

**DOI:** 10.1186/s13063-019-3896-0

**Published:** 2019-12-23

**Keywords:** Auricular acupressure, Body acupressure, Labor pain, Labor duration

## Abstract

**Background:**

Labor pain is one of the leading causes of fear of childbirth. Acupressure is a non-pharmacological pain relief method that has shown promising results in relieving this pain. The present study is designed to compare the effects of body acupressure at multiple points and auricular acupressure on the pain and duration of labor.

**Methods/design:**

In a randomized controlled trial, 90 primigravida women who attend for childbirth will be randomly assigned to one of three groups (intervention groups of either body acupressure or auricular acupressure; control, consisting of routine care). Computer-generated six-block randomization techniques will be used to determine the allocation sequence with a 1:1:1 ratio. To hide the allocation, the type of intervention will be written according to the generated sequence and put in opaque envelopes; these as well as questionnaires will be encoded. The pain score for all participants will be measured at the peak uterine contraction at 4-cm cervical dilation and at 10-cm dilation based on a visual analog scale (VAS). The duration of the active phase of labor in these groups will be recorded too. Data will be imported into SPSS-16 software. First, normality of the data distribution will be investigated. To compare labor duration among the research groups, ANOVA will be used, which will be followed, in case of significance, by the Scheffe post hoc test. Furthermore, Chi-squared test will be used to compare the categorized demographic variables and ANOVA or Kruskal–Wallis tests will be used to compare the quantitative variables in the studied groups. A significance level of 0.05 is considered significant.

**Discussion:**

In this study the effect of auricular acupressure and body acupressure on pain and duration of first stage of labor will be compared.

**Trial registration:**

Iranian Registry of Clinical Trials, IRCT20180218038789N1. Registered 2018-03-04; pre result.

## Background

Labor pain is one of the most intense pains experienced by women during their lifetime [1, 2]. Labor pain is caused by the interaction of physiological factors, such as uterine contractions and cervical dilation, and psychological factors, such as fear and anxiety [3]. Labor pain engenders an experience that most women tend to avoid and is always a source of anxiety and distress for pregnant women [4]. A considerable proportion of C-section (CS) deliveries have been performed merely due to mothers’ fear of labor pain [5].

Labor pain relief methods are divided into two major groups, namely pharmacological and non-pharmacological [6]. The most common technique for relieving pain of labor is the use of medications. However, the potential side effects of pharmacological methods for the fetus and mother have resulted in a growing interest in the use of non-pharmacological labor pain relief techniques [7].

Acupressure is a non-pharmacological pain relief method based on the principles of traditional Chinese medicine. Several acupressure points on the body are for the progression of birth and reduction of labor pain; their stimulation is believed to induce stimulation of uterine contractions and, consequently, progression of birth, on the one hand, and balance of energy as well as reduction of labor pain on the other [8]. *Sanyinjiao* (SP6), *Taichong* (LV3), *Ciliao* (BL32), *Weishu* (BL21), *Shangliao* (BL31), and *Hogu* (LI4) are among the numerous points used in acupuncture and acupressure for labor induction and management [8]. Various studies have reported reduced labor pain achieved by stimulation of a single point or a combination of two points [9–12]. GB21, BL32, LI4, and SP6 are the major points commonly proposed for enhancing uterine contractions, hard and prolonged labor, and dropping improvement. Results of an observational study of women receiving acupuncture as part of their antenatal care showed a 35% reduction in the use of labor induction, a 31% reduction in epidural analgesia, a 9% increase in the natural birth success rate, as well as shorter duration of labor compared to the local population rates [13]. Moreover, in a systematic review conducted to investigate the effect of acupressure on the onset and duration of labor, Mollart et al. reported acupressure could significantly reduce labor duration in the intervention group compared to the standard care and control groups [14]. Theoretically, when labor is slow and contractions are not intense enough, cervical dilation will be slow as well. Stimulating acupoints (acupuncture and acupressure points) can yield a balanced labor by adjusting the contractions, with improved contractions leading to reduced labor duration [15].

Auriculotherapy (AT; also known as auricular therapy) is a branch of acupressure spreading throughout the world. AT is based on a long-standing tradition and was modified and updated by [name]. Also, the World Health Organization considers AT a form of microacupuncture that can affect the whole body [16]. AT comprises several types of therapy, including auricular acupuncture, electro-stimulation, and acupressure. Various studies have reported promising results when using AT for the control of pain caused by backache, [17] pelvic fractures, [18] dysmenorrhea, [19–21] and polycystic ovarian syndrome [22]. However, only a limited number of studies have been done on the effect of auriculotherapy on labor pain, and these have yielded inconsistent results. Accordingly, in Rastegarzadeh et al.’s work, auriculotherapy led to a significant reduction in labor pain among nulliparous women [23], whereas a study by Maftoni and Shimo indicated that use of auriculotherapy caused no significant reduction in the studied women’s labor pain [24].

As can be inferred from investigations, most of the studies on body acupressure have more frequently applied pressure on one or two points; only a few studies have focused on a combination of points affecting the pain and progress of labor. Furthermore, some studies have been conducted on the effect of auricular acupressure on the reduction of different pain throughout the body, the results of which have confirmed the effectiveness of this technique. However, only a few studies have addressed the effect of auricular acupressure on labor pain, yielding inconsistent results [3, 4]. Given the small number of studies on the effect of body acupressure at multiple points and auricular acupressure on the pain and duration of labor, we designed the present study. In this clinical trial, the primary objective is to compare the effects of auricular acupressure, body acupressure, and routine treatment on the pain score at the time of 4-cm and 10-cm cervical dilations. The secondary objective is to investigate the effects of the described interventions on the duration of the first stage of labor, which is defined as the time interval between the 4 cm and 10 cm cervical dilations. This is a single-center, parallel, double blinded randomized controlled trial to investigate the superiority of auricular acupressure and body acupressure compared with routine care during the first stage of labor. The allocation ratio for the groups is 1:1:1.

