### Informed consent process

The first author will explain the research objectives and method to pregnant women meeting the inclusion criteria at the time of their admission to the labor and birth ward. The first author will then obtain written consent from patients willing to participate in the trial.

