### Randomization and blinding

A person not involved in the study will use the computer-generated six-block randomization technique to determine the allocation sequence with a 1:1:1 ratio. In order to ensure allocation concealment, this person will write the type of intervention based on the predetermined sequence and put it in an opaque envelope; these will then be encoded. The questionnaires are encoded as well. Accordingly, for a participant receiving the intervention in a pocket encoded with “1”, a questionnaire with the same code will be completed. To observe blinding during data collection, one of the coworkers will perform the intervention plan and another coworker who knows nothing about the intervention will collect the data. Finally, once the questionnaires are gathered and their data are imported into SPSS-16 software, it will be determined which codes should be assigned to group A and which codes to group B or C. Afterwards, analysis of the data will be performed. The person performing the data analysis will also be blind to the type of intervention used for each group (Fig. 1).

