#### Administration of intervention

Selection of acupoints is based on ear and body microsystems and meridians. Some treatment plans include a combination of some acupoints for every problem. These selections of points were originally derived from treatment plans developed in China, but modified by auriculotherapy discoveries in Europe and the United States. Theoretically, every acupoint can exert some identified effect for the selected condition [27–30]. For the present research, a set of primary and master acupoints was selected. Using combination sets of points is proposed to be more effective than single points. As there is scant evidence on the efficacy of applying multiple acupoints, we aim to investigate the efficacy of multiple acupoints on labor pain and duration.

In the body acupressure group, pressure is applied to the GB30, GB21, BL32, LI4, and SP6 points [13, 29] (Fig. 2) by a researcher who has been well trained for this purpose. The GB21 point has an action of release and descent, which is purported to facilitate fetal descent in the active phase and second stage of labor [31]. Stimulating the LI4 point is effective for reduction of labor pain and promoting stronger and/or more coordinated contractions [9, 32–34]. Stimulating BL32 is effective for the reduction of labor pain and induction of labor [35, 36]. One of the most important and frequently used points for obstetric and gynecologic concerns is SP6. Indications of this point include labor augmentation, for irregular contractions to encourage efficient labor and reducing a persistent cervical lip [37–39], reduction of labor pain [34, 38–41], and reduction of the length of labor [34, 38]. To perform the acupressure on the specified points on the body, each point will be pressed by the thumb for 2 min, so that one-third of the nail bed becomes white. Pressure to these points would be applied at 4, 6, and 8-cm dilations.

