**Fig. 2 Fig2:**
[figure not shown]
Body acupoints

In the auricular acupressure group, pressure will be applied to the master auricular points on the external ear (point zero, Shen Men point, and thalamic point) and primary auricular points (uterus points 1 and 2, external genitalia point, oxytocin and/or prostaglandin points) [27] by a well-trained researcher. Ear acupoints are shown in Fig. 3. The master points are so identified because they are typically active in most patients and they are useful for the treatment of a variety of health disorders. Point zero brings the whole body toward homeostasis, producing a balance of energy, a balance of hormones, and a balance of brain activity and is frequently combined with the Shen Men point for treatment of most health disorders. The purpose of Shen Men is to tranquilize the mind and to facilitate a state of harmony, serenity, and a deeper connection to one’s essential spirit. This master point alleviates stress, pain, tension, anxiety, depression, insomnia, restlessness, and excessive sensitivity. The thalamic point affects the relay of sensory information to the cerebral cortex and modulates hypothalamic regulation of autonomic nerves and endocrine glands. It is also used for alleviating most pain disorders, both acute and chronic. Primary auricular points are the most effective set of auricular points for the treatment of a health disorder in a particular body organ or for a physiological dysfunction [27]. The given pressure will be applied using an adhesive containing auriculotherapy-specific Vakharia seeds. Furthermore, auricular stimulation at the specified points will be performed every 30 min. It should be noted that the comparator group will receive routine care (Fig. 4).

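### The trial is labelled double blinded, but only the data collector and analyst are described as masked; the women, who rate the primary pain score themselves, are not

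*Protocol article*

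**What the plan says.** The design statement at the end of the Background (protocol article) reads: "This is a single-center, parallel, double blinded randomized controlled trial". It sets the aim as superiority of each acupressure method over routine care.

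Randomization and blinding then says who is masked. One coworker delivers the intervention and "another coworker who knows nothing about the intervention will collect the data". For the analyst: "The person performing the data analysis will also be blind to the type of intervention used for each group". The groups reach the analyst under the letters A, B and C. The section does not say that the women or the person giving the treatment are masked.

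Administration of intervention describes the arms:
- **Body arm:** five points, where "each point will be pressed by the thumb for 2 min", at 4, 6 and 8 cm dilation.
- **Auricular arm:** "The given pressure will be applied using an adhesive containing auriculotherapy-specific Vakharia seeds", and "auricular stimulation at the specified points will be performed every 30 min".
- **Control arm:** "the comparator group will receive routine care". No sham procedure is described.

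Before enrolment, under Informed consent process, "The first author will explain the research objectives and method to pregnant women meeting the inclusion criteria". Under Assessments and Primary outcome measurements, the primary outcome is pain intensity at 4 and 10 cm, taken with a VAS ruler.

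**The concern.** Readers commonly take a double-blind label to mean that the participants do not know their treatment. Here the participant is also the rater of the primary outcome. Masking the coworker who writes the number down does not mask the woman who gives it. The Background itself attributes labor pain partly to fear and anxiety, so by the protocol's own account the score can respond to attention and expectation.

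What is at stake is the interpretation of a positive result. A lower score than under routine care could come from the chosen points, from a trained person's attention, from expectation, or from a mixture. The label suggests that this has been controlled. Administration of intervention also speaks of efficacy of a combination of points, which invites a point-specific reading. The comparison with routine care alone cannot support that reading.

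There is a second, smaller issue. The collector is said to be unaware of the intervention, but nothing describes how that is kept up when one arm has material stuck to the ear.

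**Working it through.** The masking question is textual. The protocol gives no figure to reproduce.

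**Step 1: who is masked, by role**

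| Role | What the protocol article says | Assessment |
|---|---|---|
| Woman (rates the VAS) | No masking stated; method explained before consent; three perceptibly different treatments; no sham | Unmasked (close inference from the design) |
| Intervention provider | Carries out the allocated treatment | Unmasked by necessity |
| Data collector | Said to know nothing about the intervention | Asserted; no safeguard described for the auricular arm |
| Analyst | Blind to treatment, group letters used | Stated, and nothing contradicts it |

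The two masked roles exclude the person whose judgement is the primary outcome.

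**Step 2: the collector**

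Seeds are fixed to the external ear and stimulated every 30 minutes, and the pain score is taken again at 10 cm. A collector at the bedside would probably see them. This is an inference, because the article does not say whether ears are covered. It concerns the auricular arm only, since no lasting mark is described for thumb pressure.

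**Step 3: illustration of size**

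Inputs from the protocol article:
- SD 1.4, 30 per group and 10% dropout (Sample size estimation), so 30 × 0.9 = 27 per arm if dropouts are not analysed
- one-way ANOVA at 0.05 (Data analysis)

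Input that is assumed and not in the documents: a shift of b = 0.3, 0.5 or 0.7 VAS points in reported pain in both active arms, from expectation or attention, with no acupoint-specific effect.

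The arm means relative to control are 0, −b, −b, and their average is −2b/3. The squared deviations sum to (4/9 + 1/9 + 1/9)b² = 2b²/3. The noncentrality is

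λ = n × (2b²/3) / SD²

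For n = 27 and b = 0.5: λ = 27 × (2 × 0.25/3) / 1.96 = 4.5/1.96 = 2.30. The probability of significance is the chance that a noncentral F with 2 and 3n − 3 degrees of freedom exceeds its 5% critical value (3.11 for 2 and 78; 3.10 for 2 and 87).

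| Assumed shift b | λ, n = 27 | P(significant), n = 27 | λ, n = 30 | P(significant), n = 30 |
|---|---|---|---|---|
| 0.3 | 0.83 | 0.115 | 0.92 | 0.123 |
| 0.5 | 2.30 | 0.246 | 2.55 | 0.270 |
| 0.7 | 4.50 | 0.445 | 5.00 | 0.489 |

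The columns for 30 per arm are the closer match if the planned intention-to-treat analysis with multiple imputation keeps everyone, though imputed outcomes do not carry full information. All three shifts are below the 1-point MCID in the sample size section.

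**The case against.** The strongest reply is that the article defines its own term. Randomization and blinding names the two masked parties and never claims that the women are masked, so the fault would be a loose label rather than a broken promise. In addition, the stated question is superiority over routine care. That is an add-on comparison and needs no sham.

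Much of this stands:
- The add-on comparison is legitimate, and nothing here invalidates it.
- A reader might infer that no masking exists for the primary outcome. That goes too far. Analyst masking is stated, is not contradicted, and covers the primary analysis.
- A reader might take it as fact that the collector sees the seeds. The article does not say so.
- A reader might suppose that control women receive no touch or support. The content of routine care is not described.
- A reader might treat the percentages above as inflated type I error. Under the add-on question, expectation is part of the effect, so those rejections are not false positives. They are misleading only if read as evidence for the points themselves.
- In the comparison of auricular with body acupressure, an expectation shift common to both arms cancels.

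The reply does not rescue the label. A fuller protocol could describe a safeguard for the collector, but it could not make the women blind to the treatments described here.

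**Conclusion.** The concern holds as a matter of labelling and interpretation. The design is called double blinded, yet the masking described covers the collector and the analyst only. The women and the provider are unmasked, and the women supply the primary outcome. This rests on the close inference that a woman told the method beforehand can tell thumb pressure, ear seeds and routine care apart.

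For the collector, the conclusion is weaker: masking is asserted, is probably compromised in the auricular arm, and has no described safeguard.

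On size, an assumed shift of half the MCID (0.5 points) in both active arms would make the overall test significant in about one trial in four, with no acupoint-specific effect. The shift is an assumption, so the figure shows sensitivity and does not estimate the bias in this trial. The documents do not support concluding that the trial is unmasked throughout or that its comparison with routine care is invalid.

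**What to change.** 1. Replace the double-blind label with: data collector and analyst blinded; participants and intervention provider not blinded.
2. State that pain differences between either acupressure arm and routine care estimate the effect of adding acupressure, including attention and expectation, and not an acupoint-specific effect. Note that expectation common to both active arms cancels in the comparison between them, and that unequal expectation would not.
3. Say how the collector is kept unaware of the ear seeds. For women still to be assessed, use the same ear covering in all arms when the VAS is recorded. This protects the recorder's masking only and leaves the bias from self-report as it is.

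Items 1 and 2 cost only wording and a more modest claim, and can be done at any stage. Item 3 costs one covering per woman, but its reach is limited. Trial status gives recruitment from August 2018 and probable completion of data collection in December 2019, the month of publication, so few women may remain. If none do, the report should say that collector masking in the auricular arm could not be assured.

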## Methods/design

### Research setting and design

The present randomized controlled trial with parallel control group will be conducted on 90 pregnant women referring to Kowsar Hospital in Qazvin for labor that agree to participate in the study and meet the inclusion criteria. Qazvin is the largest city and capital of the province of Qazvin in Iran, located 150 km (93 miles) northwest of Tehran at an altitude of about 1800 m (5900 feet) above sea level. This protocol is organized based on SPIRIT guideline. This writing guideline provides Standard Protocol Items: Recommendations for Interventional Trials. The SPIRIT checklist for present study is provided in Additional file 1. 

### Intervention and comparator

The participants are divided into three groups, body acupressure (intervention 1), auricular acupressure (intervention 2), and routine care (comparison) groups (Fig. 1).

**Fig. 1 Fig1:**
[figure not shown]
Trial flow overview

### Inclusion and exclusion criteria

#### Inclusion criteria

The inclusion criteria in the present study are primigravida women aged 19–35 years at gestational age of 37–42 weeks with a singleton pregnancy, cephalic presentation, no history of chronic diseases such as diabetes, cardiovascular disease, hypertension, hepatic and renal disorders, etc., a lack of pregnancy complications such as preeclampsia, gestational diabetes, bleeding, etc., a height above 150 cm, and admission at the beginning of the active phase (3–4 cm dilation).

#### Exclusion criteria

Refusal to continue participation in the study, receiving pain relief drugs 3 h before or during the study, labor induction or enhancement by medication, and emergency CS birth constitute the exclusion criteria of this study.

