### Sample size estimation

To calculate the minimal clinically important difference (MCID) for the duration of the first stage of labor and the pain score, we used previous study data which examined the effect of auricular [24] and body [25] acupressure on labor pain intensity and labor duration. Using the method of Wyrwich et al. [26], MCID score for significant pain reduction during labor was one score based on visual analogue scale. Using the G*Power software 3.1.9.2, α = 0.05, and power = 0.80, considering SD = 1.4 and M0 = 7.2 for the labor pain score and 10% drop out of subjects, the sample size was calculated to be 30 patients for each group.

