### Primary outcome measurements

#### Pain score in the first stage of labor

In the present study, the pain score (pain intensity) at 4- and 10-cm dilations is measured in all three groups using a VAS and then compared.

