### Data analysis

Once collected, the data are imported into SPSS-16 software. Firstly, normality of the data distribution will be investigated (via three methods, including Kolmogorov–Smirnov, histogram, and dispersion and central indices) and if the distribution of variables is not normal, then we will use an appropriate transformation. To compare the labor duration and pain score among the research groups, one way ANOVA test will be used, which will be followed, in case of significance, by Scheffe post hoc test. If there are potential confounding variables, a multiple linear regression test will be used. We will check for the assumptions and concerns of the regression model. Furthermore, Chi-squared test will be used to compare the categorized demographic variables in the studied groups. In order to compare the quantitative variables, in case of normal and abnormal distribution of the variables, ANOVA and Kruskal–Wallis tests will be used, respectively. The post hoc of these tests will be reported if needed. The study will be analyzed using an intention-to-treat (ITT) approach and using a multiple imputation strategy to account for missing outcomes in ITT. Also, apropos of the significance level, 0.05 is considered significant.

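### Exclusion criteria that include events arising after entry are not reconciled with the promised intention-to-treat analysis

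*Protocol article*

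**What the plan says.** The Exclusion criteria section of the protocol article is a single sentence. It opens with "Refusal to continue participation in the study", goes on to "receiving pain relief drugs 3 h before or during the study, labor induction or enhancement by medication, and emergency CS birth", and ends by saying that these "constitute the exclusion criteria of this study". It does not separate eligibility before allocation from withdrawal after it. Under Inclusion criteria, women are admitted at 3–4 cm dilation.

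The Data analysis section states: "The study will be analyzed using an intention-to-treat (ITT) approach and using a multiple imputation strategy to account for missing outcomes in ITT".

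For the primary outcome, "the pain score (pain intensity) at 4- and 10-cm dilations is measured in all three groups using a VAS". The secondary outcome, duration of the first stage, is defined in the Background as "the time interval between the 4 cm and 10 cm cervical dilations".

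The Sample size estimation section takes an SD of 1.4, a minimal important difference of 1 VAS point, α = 0.05 and power 0.80, and says that with "10% drop out of subjects, the sample size was calculated to be 30 patients for each group".

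**The concern.** A woman who is excluded after allocation is not analysed as randomised unless the plan says that she is kept. The article states both rules and does not connect them.

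The events listed are not incidental to the trial. Analgesia and augmentation follow from pain and slow progress, and pain and duration are the two outcomes. The protocol itself expects the interventions to act on such events. The Background cites an observational study of antenatal acupuncture with 35% less induction and 31% less epidural use. The section on administration of the intervention credits LI4 with less pain and stronger contractions, and lists augmentation among the indications for SP6. If the hypothesis is right, exclusions may well differ between arms, and the women left would no longer be randomised groups.

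Many of these women also have usable outcomes. A woman given analgesia or augmentation who reaches 10 cm has a pain score and a duration that can be recorded. Treating them as missing would discard real data.

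**Working it through.** **Timing of each listed event, given entry at 3–4 cm**

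| Event | Before entry? | After entry? |
|---|---|---|
| Refusal to continue | No | Yes |
| Analgesia in the preceding 3 h | Yes | No |
| Analgesia during the study | No | Yes |
| Induction or augmentation by medication | Possible (no time limit given) | Augmentation possible |
| Emergency caesarean | No | Yes |

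Three events arise only after entry, and one more can. No sentence in the article says that these women stay in the analysis set, are followed to 10 cm, or are the ones to be imputed.

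**The plan's own figure.** With difference 1 and SD 1.4, n per group = 2(z_α + z_β)² × 1.4² / 1².
- Two-sided: 2 × (1.960 + 0.842)² × 1.96 = 30.8, so 31; divided by 0.9, 35.
- One-sided: 2 × (1.645 + 0.842)² × 1.96 = 24.2, so 25; divided by 0.9, 28.
- One-way ANOVA with means 7.2, 6.2, 6.2: 30 before dropout, 34 after.

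After the dropout allowance, only the one-sided version comes within 2 of the stated 30. That is a separate matter. It matters here only because there is little slack.

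**Power if the women are lost** (two-sided t-test, difference 1, SD 1.4):

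| Women left per arm | Loss | Power |
|---|---|---|
| 30 | 0% | 77.6% |
| 27 | 10% | 73.1% |
| 24 | 20% | 67.8% |
| 21 | 30% | 61.7% |

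**Illustration of selection.** The removal rates are assumptions, because the article gives none. If a fraction p of an arm is removed on a tendency that correlates ρ with pain, the mean of those left falls by ρ × 1.4 × φ(z)/(1 − p), where z is the upper-p normal quantile. At ρ = 1:
- p = 0.20: 1.4 × 0.2800/0.80 = 0.490
- p = 0.10: 1.4 × 0.1755/0.90 = 0.273
- p = 0.30: 1.4 × 0.3477/0.70 = 0.695
- p = 0.15: 1.4 × 0.2332/0.85 = 0.384

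For a true difference of 1.0:

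| Removed, routine care vs acupressure | ρ = 1 | ρ = 0.5 |
|---|---|---|
| 20% vs 10% | 1 − (0.490 − 0.273) = 0.78 | 1 − 0.5 × 0.217 = 0.89 |
| 30% vs 15% | 1 − (0.695 − 0.384) = 0.69 | 1 − 0.5 × 0.311 = 0.84 |

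**A second model** does not fix the ratio between arms. A woman is removed when a latent need, correlated ρ with her pain, passes a threshold common to all arms. By simulation:

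| ρ | Acupressure women removed when 20% of controls are | Difference left | Difference left when 40% of controls are removed |
|---|---|---|---|
| 0.3 | 14.5% | 0.97 | 0.95 |
| 0.5 | 11.5% | 0.91 | 0.87 |
| 0.8 | 7.9% | 0.79 | 0.68 |

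Under these assumptions the attenuation runs from negligible to about a third.

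**The case against.** The strongest reply is that the exclusion list can be read as a withdrawal list: the woman stops the intervention, stays in the intention-to-treat set, and has her outcome imputed. A reader might infer that the two rules cannot both be followed, and this reading shows that they can. It stands as a possible reading, but the article does not state it. It would also still impute over outcomes that could have been observed in women who reach 10 cm.

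A reader might also infer that all the listed events occur after randomisation. The text does not support that. Induction or augmentation carries no time limit and may already be under way at 3–4 cm, and the 3-hour analgesia clause is an ordinary eligibility criterion. The flow chart and schedule are not available here.

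Nor can one say that the imputations would borrow from women with easier labours. The imputation model is not given, an article may leave it to a fuller document, and the 4-cm score taken in all women could enter it.

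Finally, analysing observed scores has its own cost. Assume that analgesia is given to 20% of routine-care and 10% of acupressure women and lowers the VAS by 1, 2 or 3 points. A true difference of 1.0 then becomes 1 − 0.10 × 1 = 0.9, 0.8 or 0.7, comparable to the loss from exclusion. This objection stands: the remedy is a choice of estimand and must be declared as one.

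**Conclusion.** The point holds as an unreconciled conflict between two stated rules, and it should be settled because it determines who is in the primary comparison. Three exclusion events arise only after entry, a fourth can, and the article does not keep these women in the analysis. Applied as written, the exclusions would select on events tied to the trial's own outcomes.

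The direction and size of the bias cannot be known from the document. It is tempting to conclude that routine-care women with the worst pain will be lost preferentially, that a real benefit will be hidden, or that the 10% dropout allowance will be used up. Each of these needs event rates that the article does not give, and other mechanisms could act differently. The figures of about 0.7–0.8 (removal tracking pain perfectly) and 0.84–0.89 (correlation 0.5), against a true 1.0, rest on assumed pain-driven removal that is twice as common in routine care. Confidence is high for the inconsistency only.

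**What to change.** - Limit the exclusion criteria to facts known before allocation.
- Analyse every randomised woman in her allocated arm, using the observed 10-cm VAS and duration where they exist, whatever analgesia or augmentation she received. The exception is a woman who withdraws consent to the use of her data.
- State that this estimates a treatment-policy effect, and report analgesia, augmentation and caesarean rates by arm beside it.
- Use multiple imputation only for outcomes that could have been observed but were not recorded.
- State separately how a caesarean before 10 cm is handled. The 10-cm VAS and the 4-to-10-cm duration then do not exist, so they are not merely unrecorded. One option is a prespecified intercurrent-event strategy, with duration censored at caesarean as a sensitivity analysis.
- Give the analysis without these women only as a labelled sensitivity analysis.

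These changes concern the analysis set and data collection, not clinical care.

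**Cost.** No extra patients are needed, but outcome forms must be completed for women who would otherwise be dropped. The estimated effect may be diluted by analgesia or augmentation. Recruitment began in August 2018 and data collection was expected to end in December 2019, the month of publication. Scores at 10 cm that were not taken from women already dropped therefore cannot be recovered and must be reported as missing, by arm.
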